
#### Sleep subjective measurements

Sleep diary: During the 2 weeks of actigraphy data acquisition, participants will fulfil a sleep diary (either electronic or paper version) and register any potential event that may potentially impact the quality or interpretation of the data (see online supplemental material for a full description of the data collected).Sleep questionnaires: We will use the Pittsburgh Sleep Quality Index, the Insomnia Severity Index and the Epworth Sleepiness Scale to measure sleep quality, insomnia symptoms and excessive daytime sleepiness, respectively.^82–84^ We will screen for the presence of REM-sleep behaviour disorder and restless legs syndrome with single-question formularies.^85 86^

#### CSF and blood samples

CSF and blood sampling and processing will be performed as described elsewhere,^71 74^ and the following measurements will be performed:

Orexin-A determination: Orexin-A levels in CSF will be measured at the Clinical Neurochemistry Lab of the University of Gothenburg using an in-house radioimmunoassay method, as described elsewhere.^87^Core AD and glial markers: CSF total-tau and phosphorylated (P181)-tau will be measured with the electrochemiluminescence immunoassays Elecsys (Roche Diagnostics International). The rest of the biomarkers (Aβ42, Aβ40, neurogranin, neurofilament light, YKL-40, sTREM2, GFAP and S100) will be measured with the NeuroToolKit (Roche Diagnostics International), as previously described.^74^ All measurements will be performed at the Clinical Neurochemistry Laboratory, Sahlgrenska University Hospital, Mölndal, Sweden.*APOE* genotyping: *APOE* genotype determination has been performed as explained elsewhere in all ALFA+ participants.^71^

#### Neuroimaging

MRI: Scans will be obtained with a 3 T scanner (Ingenia CX; Philips, Amsterdam, Netherlands). Images will be processed with Statistical Parametric Mapping (SPM) software for volumetric and functional analyses. Volumetric analyses will be performed through voxel-based morphometry using SPM general linear models. FreeSurfer V.6.0 software will be used to calculate the volume and cortical thickness in different regions of interest. Diffusion data will be analysed through tract-based-spatial statistics, implemented in FMRIB Software Library software. Seed-based and multivariate analyses, including an independent components analysis, will be used to evaluate data from task-free fMRI and to derive functional connectivity matrices.Amyloid PET: ^18^F-Flutemetamol uptake will be calculated using the Centiloid method.^88^ Additionally, scans will also be quantified regionally and categorised as either positive or negative according to visual reading following standard procedures.Tau (PET): Retention of ^18^F-RO6958948 in brain regions and voxel-based analysis of ^18^F-RO6958948 will be measured by in vivo PET. Thresholds for positivity will be applied and ^18^F-RO6958948 uptake will be categorised according to such values.

#### Clinical variables

Neuropsychological testing: Cognition will be evaluated through a comprehensive neuropsychological battery, covering the main cognitive domains: (1) global cognition (MMSE, QI estimation (Word Accentuation Test)); (2) attention [Wechsler Adult Intelligence Scale (WAIS)-IV: Digit Span, Wechsler Memory Scale –Fourth Edition (WMS-IV): Symbol Span, Trail-Making Test (TMT)-A]; (3) episodic memory (Free and Cued Selective Reminding Test, Memory Binding Test, WMS-IV Logical Memory, NIH Toolbox Picture Sequence Memory Test); (4) executive function (TMT-B, Five Digits Test, WAIS-IV Coding, WAIS-IV Matrix Reasoning and NIH Toolbox Flanker Inhibition Test); (5) language (animal fluency: number of animals named in 1 min); and (7) visual processing (WAIS-IV Visual Puzzles, RBANS Judgement of Line Orientation).^89–94^Mood state: Mood state will be evaluated with the Spanish version of the Hospital Anxiety and Depression Scale.^95^Medical history, medication and lifestyle habits will be collected, including detailed neurological, psychiatric and systemic history; brief parental medical history; history of medication; and smoking, alcohol and drug consumption, physical exercise and dietary habits.Anthropometric measurements and vital signs will be acquired, including weight, height, waist diameter, body mass index (BMI), blood pressure and heart rate.Sex-specific variables including age at menopause, use of sexual hormones (oestrogens) to treat menopause symptoms and/or contraceptive medications, together with a history of surgeries and medication will be acquired.

### Statistical analyses

Data will be inspected to check normality assumptions and identify outliers. We will analyse associations between the following predictors: (1) objective (actigraphy, nasal flow monitoring device and PSG) and subjective sleep-related measures and (2) CSF–orexin-A levels; and the following dependent variables: (1) CSF AD and glial biomarkers, (2) neuroimaging and (3) cognitive performance outcomes. We will also analyse between-group differences in these predictors among different biomarker categories (AT profiles). These analyses will be adjusted by potential confounders (eg, age, sex, *APOE* genotype, education, anxiety/depression, BMI, sleep apnoeas and/or others) as appropriate. Additional interaction analyses may be performed to test whether *APOE* genotype or sex modify any of these associations. Mediation analyses will be used to evaluate whether associations between sleep-related metrics and brain structure and function are driven by AD and/or glial activity biomarkers. In addition, we will compute receiver operating characteristic curves and use the Youden Index (J=sensitivity+specificity–1) to derive optimal cut-off values for objective sleep measurements to discriminate between individuals with normal versus altered AD biomarkers. We will use general linear models to test associations involving continuous dependent variables and analysis of covariance (ANCOVA) to assess between-group differences among AT profiles. Non-parametric equivalents will be used if required model assumptions are not met.

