### Hypotheses and aims

Our main hypotheses are (1) altered sleep patterns (including altered sleep macroarchitecture (eg, abnormal sleep duration, efficiency or fragmentation) and microarchitecture (eg, decreased SWA or spindle expression)) and OSA are associated with higher AD pathology and neuroinflammation levels (the latter after accounting for AD pathology); (2) higher CSF–orexin-A levels are associated with abnormal AD biomarkers; (3) altered sleep patterns and OSA are associated with brain structural differences involving AD vulnerable areas and worse cognitive performance; (4) association of altered sleep patterns and OSA with neuroimaging and cognitive outcomes is partially mediated by AD biomarkers and neuroinflammation; and (5) associations between CSF–orexin-A and AD biomarkers are mediated by changes in sleep architecture. To test these hypotheses, we will characterise 200 cognitively unimpaired participants from the ALFA+ study with actigraphy measurements, nasal flow monitoring devices and CSF–orexin-A levels, and a subgroup of 90 participants with overnight polysomnography (PSG). We will also explore the potential usefulness of objective sleep measurements to predict the presence underlying AD pathology.

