#### Sample size calculation

The sample size has been computed with G*Power V.3.1.9.4,^96^ taking into account the estimated effect size (ES) of a previous study using a similar methodology for the detection of differences in sleep efficiency between cognitively unimpaired individuals with normal versus abnormal Aβ biomarkers.^24^ For this ES (ES=0.49), we calculate that a sample size of n=178 (89 cases/89 controls) would be enough to achieve a statistical power of 90%, assuming a 5% type I error probability (two tails) (figure 2).

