**Figure 2 F2:**
[figure not shown]
Estimation of statistical power as a function of sample size.

Based on these estimations, we plan to recruit 200 subjects: 100 with altered Aβ biomarkers and 100 with normal biomarkers. The sample size for the exploratory PSG substudy (n=90) is based on previous literature.^44^

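### Sensitivity, specificity and J at the Youden-derived sleep cut-offs will be overstated if they are reported, uncorrected, in the participants used to find the cut-offs

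*Protocol article*

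**What the plan says.** The Statistical analyses section of the protocol article states that ROC curves will be computed and the Youden Index (sensitivity + specificity − 1) used "to derive optimal cut-off values for objective sleep measurements to discriminate between individuals with normal versus altered AD biomarkers". The object is plural. Under Sleep objective measurements the article lists six main actigraphy measures, and adds circadian, respiratory and polysomnography (PSG) measures.

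The aim behind this analysis follows the five main hypotheses and is framed as exploratory: "We will also explore the potential usefulness of objective sleep measurements to predict the presence underlying AD pathology".

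The samples available are those of the study itself. For the main sample, "we plan to recruit 200 subjects: 100 with altered Aβ biomarkers and 100 with normal biomarkers". For PSG, "The sample size for the exploratory PSG substudy (n=90) is based on previous literature", and Study population gives its mix as roughly one third each of A−T−, A+T− and A+T+. The formal sample size rests on a mean difference in sleep efficiency, not on ROC accuracy: "For this ES (ES=0.49), we calculate that a sample size of n=178 (89 cases/89 controls) would be enough".

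No second sample, hold-out, cross-validation or bootstrap correction is mentioned. Nor does the article say that accuracy will be reported uncorrected.

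**The concern.** The Youden cut-off is the threshold at which the observed sensitivity plus specificity is largest. Part of that maximum is chance. Accuracy read at the same threshold in the same people keeps the chance part, and a new sample would not. The effect grows as groups shrink, and grows again if several markers are searched and the best one is highlighted.

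The Abstract and the Discussion both name non-invasive biomarkers as a goal, so a published cut-off with its sensitivity and specificity invites reuse. The reader would take from it a better account of how well sleep separates the biomarker groups than the data support. In the PSG subset, the bias is large relative to the signal the study expects.

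**Working it through.** **Inputs from the protocol.** Effect size 0.49, two-sided 5% type I error, 90% power, 89 per group (Sample size calculation). Planned groups 100 v 100. PSG subset of 90 in thirds: 30 A−T− against 30 + 30 = 60 A+, that is 30 v 60.

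**Assumptions not in the protocol.** Normal markers with equal variance in both groups. Where several markers are compared: 6 or 12 of them, correlation 0 or 0.5, the same effect size for each, and direction chosen from the data.

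**Step 1. The plan's own figure.** The normal approximation gives n per group = 2(1.960 + 1.282)² / 0.49² = 87.5, so 88. The noncentral t-test gives power 0.898 at 88 and 0.902 at 89 per group. The stated 178 (89 per group) is therefore reproduced. With 100 per group, power for the mean difference is 93.2%.

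**Step 2. What an effect size of 0.49 means for discrimination.**
- AUC = Φ(0.49/√2) = 0.636.
- Best attainable J = 2Φ(0.49/2) − 1 = 2(0.597) − 1 = 0.194, with sensitivity = specificity = 0.597.

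**Step 3. One marker, direction fixed in advance.** In each of 4,000 simulated studies, the cut-off with the largest observed J was chosen. Its observed J was compared with the J that the same cut-off truly achieves in the population.

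| Groups | Effect size | Mean apparent J | Mean true J | Excess | Mean AUC |
|---|---|---|---|---|---|
| 100 v 100 | 0.49 | 0.248 | 0.179 | 0.069 | 0.636 |
| 100 v 100 | 0.25 | 0.163 | 0.087 | 0.077 | 0.570 |
| 100 v 100 | 0 | 0.084 | 0 | 0.084 | 0.499 |
| 30 v 60 | 0.49 | 0.287 | 0.172 | 0.115 | 0.636 |
| 30 v 60 | 0.25 | 0.205 | 0.082 | 0.123 | 0.570 |
| 30 v 60 | 0 | 0.130 | 0 | 0.130 | 0.500 |

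At an effect size of 0.49, the relative overstatement is 0.069/0.179 = 39% in the main sample and 0.115/0.172 = 67% in the PSG subset. The mean AUC equals its true value of 0.636 in both.

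**Step 4. Best of several markers** (1,000 simulated studies for each setting; ranges cover 6 to 12 markers and correlation 0 to 0.5).

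| Groups | Effect size | Apparent J of the best | True J | AUC of the best (true AUC) |
|---|---|---|---|---|
| 100 v 100 | 0.49 | 0.31–0.35 | about 0.19 | 0.67–0.70 (0.64) |
| 100 v 100 | 0 | 0.16–0.19 | 0 | 0.56–0.58 (0.50) |
| 30 v 60 | 0.49 | 0.38–0.43 | about 0.18 | 0.70–0.73 (0.64) |
| 30 v 60 | 0 | 0.26–0.29 | 0 | 0.60–0.63 (0.50) |

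Once a best marker is picked, the AUC is biased upward too. In the PSG subset, the best of six or more uninformative markers shows a mean apparent J above 0.194, the most that a marker with the planned effect could truly reach.

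**Step 5. How good the chosen cut-off is.** As a share of the attainable J, the selected cut-off delivers 0.179/0.194 = 92% (100 v 100) and 0.172/0.194 = 89% (30 v 60). The reported accuracy is what goes wrong; the threshold itself loses little.

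**The case against.** The strongest reply is that the article is a condensed protocol without its analysis plan. Resampling, intervals for cut-offs and comparator models are details usually left there. The article does not say that accuracy will be reported in the same people, or that a best marker will be picked. This stands in part, and it is why the conclusion is conditional. It does not remove the point. The method the article names is a data-searched cut-off, the only sample described is the study's own, and correction would improve that stated method.

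A second reply is that the aim is exploratory. This also stands. It limits the weight of the point and argues for saying so beside each cut-off.

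Four stronger readings are tempting, and the documents do not support them:
- A reader might infer that discrimination as a whole will be overstated. The AUC of a single prespecified marker is unbiased; the bias lies in J, sensitivity and specificity at the searched cut-off, and in the AUC only after marker selection.
- A reader might infer that the cut-offs would fail elsewhere. In new people from the same population they keep about nine tenths of the attainable J.
- A reader might infer that leaving out A−T+ people flatters the results. Table 1 shows 13 such people (3.3%), too few to matter much.
- A reader might infer that PSG cut-offs should not be reported without external validation. For an aim and a substudy both described as exploratory, that is a preference rather than a defect in the plan.

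The absence of a stated age, sex and *APOE* comparison model is a separate question. It bears on whether sleep adds anything to what is already known about a person, not on optimism of the cut-off.

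**Conclusion.** The point holds in conditional form. If sensitivity, specificity and J are reported uncorrected at Youden cut-offs in the participants who supplied those cut-offs, mean J at the planned effect size is too high by about 0.07 in the main sample and about 0.12 in the PSG subset. A marker with no information would show about 0.08 and 0.13. If the best of several markers is highlighted, both its J and its AUC are inflated further.

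The single-marker figures rest on normal, equal-variance markers. The excess changes little between effect sizes of 0.25 and 0.49. The best-of-several figures rest also on an assumed number and correlation of markers, so they show a range and do not predict what this study will report. This is a modest change to an exploratory analysis; it does not touch the main hypotheses or the sample size.

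**What to change.** - Report bootstrap optimism-corrected sensitivity, specificity and J beside the apparent values. Repeat the cut-off search in every resample.
- If markers are compared and one is highlighted, repeat that selection in every resample as well, and correct its AUC in the same way.
- Give a confidence interval for each cut-off.
- Label all cut-offs exploratory, most clearly those from PSG.
- As a supplementary analysis, report the gain in AUC from adding the sleep measure to a model with age, sex and *APOE*. The article already names these as possible adjustment variables and they are already collected.

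The cost is a short piece of analysis code and a few sentences in the analysis plan, with no new data and no change to recruitment. The downside is that the reported accuracy will look slightly less favourable.

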#### Sample size calculation

The sample size has been computed with G*Power V.3.1.9.4,^96^ taking into account the estimated effect size (ES) of a previous study using a similar methodology for the detection of differences in sleep efficiency between cognitively unimpaired individuals with normal versus abnormal Aβ biomarkers.^24^ For this ES (ES=0.49), we calculate that a sample size of n=178 (89 cases/89 controls) would be enough to achieve a statistical power of 90%, assuming a 5% type I error probability (two tails) (figure 2).

**Figure 2 F2:**
[figure not shown]
Estimation of statistical power as a function of sample size.

Based on these estimations, we plan to recruit 200 subjects: 100 with altered Aβ biomarkers and 100 with normal biomarkers. The sample size for the exploratory PSG substudy (n=90) is based on previous literature.^44^

### Patient and public involvement

Participants and the public were neither involved in the study design, recruitment or conduct, nor in the selection of research questions or study outcomes. All participants will receive feedback related to their usual sleep patterns. In case any clinically relevant finding is detected in the context of their participation, participants will receive a specific report describing such findings, as well as clinical counselling. Additionally, with the support of the communication unit at BBRC, we will develop specific activities to participate in public engagement initiatives. BBRC is fully aware of the importance of, and is committed to, involving the public as an active stakeholder of its research activities. As such, BBRC researchers lead and participate in diverse research-related communications and public awareness initiatives focused on increasing awareness about AD and the research that is being developed. BBRC will also include the profile of any proposed action at the institutional website, which is regularly updated as the research progresses.

### Ethics and dissemination

The ALFASleep study protocol has been approved by the independent Ethics Committee Parc de Salut Mar, Barcelona (2018/8207/I). All participants have signed a written informed consent before their inclusion (approved by the same independent ethics committee). Study findings will be presented at national and international conferences and submitted for publication in peer-reviewed journals.

## Discussion

Studies analysing the association between sleep and AD are gaining *momentum* since sleep represents both an appealing target for interventions aimed to prevent cognitive impairment and for the development of non-invasive diagnostic and prognostic biomarkers for AD. However, many studies published so far rely on subjective sleep quality scales, which are valuable clinical tools but may not be an ideal marker for incident dementia risk.^97^ Conversely, objective sleep measurements, such as actigraphy or PSG, provide unbiased, measurable and multidimensional sleep-quality data. Therefore, to gain a better understanding of the mechanisms underlying the association between sleep and cognitive impairment, there is a need for multimodal studies in cognitively unimpaired adults combining not only subjective but also objective sleep measures, with fluid biomarkers (encompassing AD and glial activation biomarkers, as well as CSF orexin levels), neuroimaging and cognitive data. Due to its multimodal approach and the profile of the study population (a cohort of cognitively unimpaired middle-aged adults enriched for AD risk), the ALFASleep project has the potential to make relevant contributions to the understanding of the role of sleep as a risk factor and early clinical manifestation of AD. On top of this, the present project may be complemented in the future with additional neuroimaging processing methods or MRI sequences to quantify structural changes in key regions involved in sleep–wake cycle regulation, such as the locus coeruleus or the hypothalamus,^98 99^ as well as emerging neuroimaging techniques to investigate the glymphatic system function, one of the most relevant potential links between sleep and AD pathophysiology.^20^ In addition, taking advantage of the prospective design of the ALFA+ study, with the present project, we intend to set the basis for a longitudinal study that may help unravel bidirectional associations between sleep and AD.

However, this project has some limitations. First, its observational design does not allow us to infer causality in potential associations between sleep and AD-related outcomes. Second, the ALFA+ cohort is mainly composed of well-educated individuals with very low comorbidity burden and low ethnic diversity, which may therefore constitute a source of bias.

Nonetheless, this project has direct potential clinical applications, which are the identification of altered sleep architecture patterns that may be specifically linked with AD pathology (such as decreased SWA), as well as characterising mechanisms linking sleep disruption and AD that may be amendable to potential therapeutic interventions. Thus, the resulting evidence could be used to design an intervention study targeting sleep quality, with the ultimate goal of preventing or slowing cognitive decline.

## Data Availability

Data sharing is not applicable as no datasets were generated and/or analysed for this study. N/A.
